#### Application to PJB

Applicants for PJB are recruited using a three-tiered recruitment process, which was developed by the PJB Steering Committee: (1) referral and advertisement at healthcare providers in each neighborhood; (2) referral and advertisement at neighborhood community sites (social services offices, libraries, etc.); and (3) via social media, including the Philly Joy Bank website^2^. Individuals interested in applying for the PJB lottery do so via the PJB website, where they complete their application and receive assistance with submitting their application, if needed. Individuals can apply for the PJB lottery if they are: (a) 18 years or older; (b) between 12 and 24 weeks pregnant; (c) self-attest to household income of ≤100 K per year; and (d) live in one of the three target neighborhoods. The PJB program manager and navigator confirm each applicant’s eligibility for PJB before applicants are recruited to participate in the evaluation research study or entered into the lottery. See Figure 2 for a visual of the timeline of PJB application, lottery selection, and research study enrollment.

**Figure 2 fig2:**
[figure not shown]
Process of selecting applicants for program and evaluation.

#### Lottery selection process

All eligible applicants are subsequently entered into a lottery to enroll in PJB (cash + care). The PJB Steering Committee voted on selection via lottery for three reasons. Specifically, they felt that (1) interest in PJB would exceed availability; (2) random selection would reduce bias in selection of participants; (3) it was difficult to determine who is most “deserving” of the money given high needs across most of the eligible population. Everyone who is selected into PJB via the lottery receives “cash + care,” a monthly cash disbursement and optional financial counseling and care services (doula, lactation, home visiting). Individuals who are not selected are eligible to receive “care” i.e., optional financial counseling and care services. Eligible applicants for PJB are selected at a probability that was determined by the PJB Steering Committee stratified by neighborhood. Random selection takes place every 2 weeks using the current eligible applicant pool for the PJB until 250 participants are selected by lottery to receive cash + care. An applicant may be entered into a second lottery draw if they are still eligible (by gestational age) at the time of the second lottery. At each lottery draw, the PJB implementation team utilizes a neighborhood-stratified simple random sample method to select eligible applicants from each neighborhood. Individuals who are selected for PJB are notified via automated text and email, then a phone call by the PJB Navigator and given 2 weeks to enroll in PJB. Enrollment of 250 participants into PJB began in June 2024 and was completed in March 2025.

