Explore the preliminary impact of PJB on parental mental health and prematurity. The purpose of the PJB is to reduce disparities in birth outcomes. Given the limited numbers of participants in this pilot program and evaluation study, however, we are underpowered to examine such disparities. Consequently, birth outcomes are included as exploratory analysis for potential signals of GI impact. Another important outcome for the PJB evaluation study is perinatal depression, which we do have sufficient statistical power to examine. Perinatal depression is also associated with adverse birth outcomes and can be a marker for perinatal health.

To investigate post-baseline differences in continuous EPDS depression score in the cash + care and care groups, our primary analyses will use mixed effects regression models with fixed effects for time (baseline, 6 months postpartum and 12 months postpartum), group, and the interaction between time and group and random participant-level intercepts. Using these models, we will estimate and report the average difference in depression score between groups over follow-up with 95% confidence intervals. We will also characterize outcome patterns over time by presenting estimated mean outcomes at each time point individually. We will use the same approach to examine post-intervention differences anxiety score. In secondary analyses, we will examine differences in infant birthweight and preterm birth in the cash + care vs. care groups using logistic regression. Birthweight and gestational age at birth will be determined using data from birth records and classified as low birthweight <2,500 grams (y/n) and preterm birth <37 weeks (y/n). We will examine the sensitivity of our findings to the inclusion of key potential confounders in our models, including SES and pregnancy-related variables (e.g., gravidity, parity, maternal health conditions).

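### The chance of being drawn for cash depends on gestational age at application through the second-draw rule, but no primary between-group model conditions on gestational age or on the lottery stratum

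*Protocol article*

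**What the plan says.** Under Lottery selection process, the protocol article states: "Eligible applicants for PJB are selected at a probability that was determined by the PJB Steering Committee stratified by neighborhood". It continues: "Random selection takes place every 2 weeks using the current eligible applicant pool for the PJB until 250 participants are selected". Each draw "utilizes a neighborhood-stratified simple random sample method to select eligible applicants from each neighborhood". On re-entry it says: "An applicant may be entered into a second lottery draw if they are still eligible (by gestational age" at the time of that draw. Under Application to PJB, applicants must be "between 12 and 24 weeks pregnant".

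Under Quantitative data analysis, Aim 3, the primary EPDS model has "fixed effects for time (baseline, 6 months postpartum and 12 months postpartum), group, and the interaction between time and group and random participant-level intercepts". Anxiety uses the same approach. The secondary analyses examine "differences in infant birthweight and preterm birth in the cash + care vs. care groups using logistic regression". Covariates enter only to test the sensitivity of the findings, as key potential confounders "including SES and pregnancy-related variables (e.g., gravidity, parity, maternal health conditions". Neighborhood, draw and gestational age at application are not named in any of these models.

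**The concern.** Selection is random among applicants in the same neighborhood at the same draw. It is not random with respect to gestational age once the draws are pooled. A care-only member has lost every draw entered, and an early applicant can enter more draws than a late one. The cash group will therefore contain more early applicants and the care-only group more late ones. This follows from the re-entry rule and needs no assumption about the size of the selection probability.

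Gestational age at application also sets how much of the pregnancy is covered by cash, and it may be related to access to care or to distress. If it is related to an outcome, the unadjusted group difference mixes that relation with the effect of cash. The remedy lies in conditioning on the variables that determined the chance of selection, and the stated primary estimator leaves them out.

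**Working it through.** **The plan's own figure.** Inputs from Power and sample size: 164 and 117 participants, SD 6.24, two follow-up observations, within-participant correlation ρ of 0.3 to 0.5, two-sided alpha 0.05, power 80%.

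MDD = (1.960 + 0.842) × 6.24 × √((1+ρ)/2) × √(1/164 + 1/117)

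- ρ = 0.5: 2.802 × 5.404 × 0.1210 = 1.83 (stated 1.8)
- ρ = 0.4: 1.77 (stated 1.8)
- ρ = 0.3: 1.71 (stated 1.7)
- ρ = 0.5 after 25% dropout (123 and 88): 2.11 (stated 2.1)

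The power figures reproduce and are not in dispute.

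**One chance against two.** With per-draw probability p, the chance of ever being selected is p with one draw and 1 − (1 − p)² with two. This gives 30% against 51% at p = 0.3, 40% against 64% at p = 0.4, and 50% against 75% at p = 0.5.

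**Imbalance between groups.** Let f be the share of applicants early enough for a second draw. The documents give neither p nor f. I chose p so that about 58% are selected overall, as in the study sample (164/281 = 58.4%), and took two values of f.

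- *f = 10/12 = 83%.* This assumes application spread evenly over the 12-week window, with the last 2 weeks too late for a second draw. With p = 0.386, two draws give 1 − 0.614² = 0.623. Overall selection is 0.833 × 0.623 + 0.167 × 0.386 = 0.584. The two-chance share is 0.833 × 0.623 / 0.584 = 89% of the cash group and 0.833 × 0.377 / 0.416 = 75% of the care-only group, a gap of 13.5 points.
- *f = 50%.* With p = 0.45, two draws give 1 − 0.55² = 0.6975. Overall selection is (0.6975 + 0.45)/2 = 0.574. The share is 0.6975/1.1475 = 61% of the cash group and 0.3025/0.8525 = 35% of the care-only group, a gap of 25 points.

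**Effect on EPDS.** Bias = gap × mean EPDS difference between early and late applicants. For an assumed difference of 1 to 2 points:

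- f = 83%: 0.135 × 1 = 0.14 to 0.135 × 2 = 0.27
- f = 50%: 0.25 × 1 = 0.25 to 0.25 × 2 = 0.5

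The standard error of the group difference at ρ = 0.5 is 5.404 × 0.1210 = 0.65, so the bias is roughly 0.2 to 0.8 standard errors. Its direction is not known.

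**Cost of conditioning.** Adjusting for gestational age multiplies the MDD by about 1/√(1 − R²), where R² is the squared correlation of group with gestational age, s(1 − s)d². Here s is the share selected and d the standardised difference in gestational age. Both come from a simulation with application uniform over 12 to 24 weeks, two-weekly draws and constant p.

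- At most two draws, p = 0.4: s = 0.58, d = 0.32 (about 1.1 weeks), R² = 0.025, MDD = 1.83/√0.975 = 1.86.
- Re-entry continuing to 24 weeks, p = 0.3: s = 0.61, d = 0.85, R² = 0.17, MDD = 1.83/√0.83 = 2.01.

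**The case against.** Several counter-arguments have force.

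- **Neighborhood.** A reader might infer that the cash group is enriched for neighborhoods with a higher selection probability. The text says that the probability was set and stratified by neighborhood, not that it differs between neighborhoods. One common probability fits the wording and would balance neighborhood. Enrichment by neighborhood or draw is possible but not shown.
- **Size.** Neither the share able to re-enter nor the EPDS gap between early and late applicants is in the documents. With no such gap, this source gives no bias in EPDS. The 58% is the make-up of a voluntary study sample, not the lottery's selection rate. Larger imbalances need unlimited re-entry, whereas the article speaks only of a second draw.
- **Baseline.** EPDS is measured before any cash is paid, and baseline is a level of time in the model. A change-from-baseline contrast would remove a stable early/late difference. The article describes the average difference between groups over follow-up, which leaves the contrast open. Low birthweight and preterm birth have no baseline value, although the article calls them exploratory and underpowered.
- **Open covariate list.** Gestational age could fall under pregnancy-related variables, and a fuller plan may exist. But the article spells out the primary fixed effects and assigns covariates to sensitivity analysis, so this is a stated estimator and not an omitted detail.

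A reader might also conclude that the groups are simply not comparable. That goes too far, because selection within neighborhood and draw remains random.

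**Conclusion.** The point holds for the gestational-age mechanism. The re-entry rule ties the cumulative chance of cash to gestational age at application, and the stated EPDS, anxiety and birth-outcome models do not condition on it or on the lottery stratum.

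The imbalance in two-draw eligibility is roughly 13 to 25 points. This assumes at most two draws, about 58% selected, and 83% or 50% of applicants able to reach a second draw. The resulting EPDS bias of about 0.14 to 0.5 points rests further on an assumed 1 to 2 point gap. That is about 8 to 28% of the 1.8-point detectable difference, and less or nothing if the reported contrast is change from baseline. No size can be given for the birth outcomes from the documents. The stated power is essentially unaffected.

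**What to change.** Include neighborhood (the lottery stratum), gestational age at first draw and draw period (for example calendar quarter) as fixed effects in the primary EPDS and anxiety models. Do the same in the low-birthweight and preterm-birth models where event counts allow. State whether the EPDS contrast is the difference over follow-up or change from baseline.

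Alternatively, if draw-level records were kept and can be shared with the evaluators, weight by each applicant's cumulative selection probability over the draws for which that applicant was eligible. Do not adjust for the number of draws actually entered: it depends on the lottery result, because a first-draw winner always has one.

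The program already confirms residence and gestational age as eligibility criteria, so the main terms should need no new data collection. Draw dates have to come from program records; the article's list of monitoring data gives only counts. The statistical cost for gestational age is a detectable difference of about 1.86 instead of 1.83, or about 2.0 if re-entry is unlimited, still well below the 4-point change that the article calls clinically meaningful. Neighborhood and draw period use a few more degrees of freedom, whose cost was not calculated.

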### Part 4. Evaluation of PJB

#### Research study enrollment and retention

Prior to lottery selection, all individuals who are eligible for the lottery are also eligible (but not required) to participate in the evaluation research study. Individuals learn about the opportunity to join the study from community researchers (CR) immediately after the PJB team confirms their eligibility and prior to lottery selection. The CRs emphasize to applicants that study participation is voluntary -- lottery selection is not contingent upon participation in the study. Individuals who are interested in participating in the study provide informed consent via phone and either complete the baseline survey the same day or schedule a time for baseline survey completion within the next week. At the time of the baseline survey, approximate dates for the follow-up surveys are scheduled based on the participant’s estimated date of delivery (EDD). At enrollment into the study, participants are asked to share their phone number and their address so that we may remind them of future appointments.

Following approaches the research team has used in other studies, CRs check in with participants via phone, text message or email at a minimum of four time points to maximize retention. First, CRs do a phone check-in with participants 1 month prior to delivery and also send out a short e-newsletter around the EDD to keep participants passively engaged and foster a sense of community and commitment. Second, CRs do a text or call check-in with participants 1 month after estimated delivery to ascertain actual delivery date. CRs repeat the phone check-in approximately 1 month prior to all postpartum visits to confirm or (re)schedule the follow-up survey. Participants who miss their scheduled appointment are contacted within one business day. At least four attempts are made to contact the participant by phone, text or email, using multiple contact times to increase success (am/pm/weekend).

#### Quantitative data collection

Quantitative data collection takes place at enrollment (12–24 weeks gestation) and at 6 and 12 months postpartum (Figure 3). Participants in both groups (i.e., cash + care and care only) complete the baseline survey prior to receiving the cash disbursement, financial counseling, or care services. Survey data is collected through REDCap, a secure, web-based application that complies with HIPAA regulations. All data collection procedures follow approaches used in other local studies. Each survey is administered via an interviewer over the phone. Each question is read to the participant; responses are recorded on a tablet with a secure internet connection. All data management standards reflect the goal of reproducible research. To reduce data entry errors and omissions, we take advantage of REDCap’s built-in quality control functions. Data integrity is aided by the system’s automated logging of all input and edits. After each survey is complete, CRs send the participant a gift card (electronically or by text) and a community resource guide. Participants receive $50 for completion of the baseline survey, and the amount is increased by $25 for each subsequent survey.

**Figure 3 fig3:**
[figure not shown]
Philly Joy Bank evaluation time points.

#### Quantitative measures

Outcomes will come from multiple data sources. We will draw on PJB routine monitoring data to assess feasibility. Self-report outcomes (including reports on acceptability and satisfaction) will come from surveys. Finally, for engagement in prenatal care and birth outcomes, with consent from participants and permission from the Pennsylvania Department of Health, Bureau of Health Statistics and Registries, we will obtain individually matched birth records of study participants.

#### Feasibility and acceptability

Reach will be assessed using monitoring data collected by PDPH, and will include number of applications, number of eligible applicants, number invited to enroll, number enrolled in PJB, and number referred for care services. Dose received will be tracked by examining how many payments each participant was eligible to receive and how many they received over the course of the program. Retention of participants in the evaluation study will be reported for each evaluation time point. Acceptability will be assessed using survey items at the 12-month endline survey and participatory data.

#### Outcomes

Low birth weight will be extracted from the birth record and defined as an absolute weight of <2,500 g regardless of gestational age (27). Preterm birth will be extracted from the birth record and defined as birth prior to 37 weeks gestation (27).

Depression will be assessed using the Edinburgh Postnatal Depression Scale (EPDS), a measure validated for use during and up to 24 months after pregnancy (28–31). The scale consists of 10 items scored on a 4-point Likert scale which ask about common depressive symptoms experienced in the prior week. We will characterize this primary outcome using a continuous score because subclinical symptoms can impact functioning (32, 33). Additionally, we will characterize probable depression (yes vs. no) using a cut-off score of ≥11 (34). Anxiety will be assessed using the Generalized Anxiety Disorder scale-7 (GAD-7) score (continuous) which is a reliable and validated measure for use during and after pregnancy. The GAD-7 consists of 7 items scored on a 4-point Likert scale which ask about common anxiety symptoms in the prior 2 weeks (range 0–21).

Stress will be measured through two scales. First, perceived stress will be measured with the ten-item Perceived Stress Scale (PSS) (35). Scores range from 0–40 and will be categorized into three groups as low stress (0–13), moderate stress (14–26), and high stress (27–40). Second, parental stress will be measured using three modified subscales of The Parental Cognitions and Conduct Toward the Infant Scale (PACOTIS), including: parental self-efficacy (six items), perceived parental impact (five items), and parental overprotection (four items) (36). Items are scored from 0 to 10 with higher scores indicating higher levels of self-efficacy, parental impact, and overprotection. Mean scores for each subscale will be used for analysis. Ability to meet basic needs will be measured through three domains: financial, food, and housing insecurity. Financial insecurity will be measured using the 10-item Consumer Financial Protection Bureau Financial Wellbeing Scale (37). Continuous scores ranging from 0 to 20 will be categorized by quartiles for analysis (38). The validated, two question Hunger Vital Sign screener (39) will be used to measure households at risk of food insecurity, and housing insecurity will be assessed using up to 16 items on history of homelessness, history of eviction, and falling behind on rent and utilities. Engagement in health care will be captured using prenatal care attendance data from the birth certificates. Specifically, adequacy of prenatal care (APCNU) is assessed using the Kotelchuck index by creating a ratio of observed prenatal care visits to expected prenatal care visits, relative to the American College of Gynecology recommended standard of care, classified as inadequate, intermediate, adequate or adequate plus (40). Parent–child attachment will be assessed using the Maternal Postnatal Attachment measure, a validated continuous scale (41). The scale consists of 19 items which ask the birthing parent to reflect on their thoughts and feelings toward their baby (42).

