To assess the feasibility and acceptability of PJB, we will use routinely collected data on study engagement among potential participants and 12-month endline survey data among PJB participants. Quantitative data analysis: Feasibility: We will assess the number and proportion of participants reached by PJB by creating quarterly reports from the routine data. We will compile absolute numbers for the following: (1) # who indicate interest; (2) # invited to enroll; (3) # who enroll; (4) # who are referred for care services. Acceptability: We will describe perceived acceptability quantitatively using 11 items on spending and decision-making control and ten items about the timing of GI payments from the endline survey. Acceptability of each care service will be evaluated using six items from the endline survey and acceptability of PJB and its evaluation will be assessed using three survey items. Qualitative data analysis: We will also examine perceived acceptability in the participatory session and will analyze data following procedures in Aim 2.

###### Aim 2

Examine *whether* and *how* a guaranteed income affects parental stress, ability to meet basic needs, engagement in healthcare and bandwidth for parenting among recipients of the cash + care. Quantitative data analysis: we will use survey data to examine *whether* receiving cash + care affects outcomes using two steps. First, we will describe baseline demographic characteristics among those who receive cash + care. Second, we will examine differences in parental stress, basic needs, engagement in care and bandwidth for parenting over follow-up (baseline, 6 months postpartum, and 12 months postpartum surveys). We will use mixed effects regression models with a fixed effect for time (categorical) and random participant-level intercepts. We will examine the sensitivity of our findings to the inclusion of key potential confounders in the model, including SES and pregnancy-related variables (e.g., gravidity, parity, maternal health conditions). Using these models, we will estimate and report the average difference in outcome between groups over follow-up with 95% confidence intervals. We will also characterize outcome patterns over time by presenting estimated mean outcomes at each time point individually.

###### Aim 3

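### The financial wellbeing score is cut into quartiles for analysis and perceived stress into three bands, with no continuous analysis stated for either, although Aim 2 is to report mean outcomes

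*Protocol article*

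**What the plan says.** The Outcomes section treats its scales in two ways.

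- **Financial wellbeing:** "Continuous scores ranging from 0 to 20 will be categorized by quartiles for analysis". A reference is cited, but the text does not say which sample or which survey sets the quartiles.
- **Perceived stress:** the 0–40 PSS score "will be categorized into three groups as low stress" (0–13), moderate (14–26) and high (27–40). No other use of the score is described.
- **Depression (EPDS):** "We will characterize this primary outcome using a continuous score because subclinical symptoms can impact functioning". A cut-off of 11 or more is added as a supplement.
- **Anxiety (GAD-7):** named as a continuous score.
- **Parental cognitions (PACOTIS):** "Mean scores for each subscale will be used for analysis".

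The Aim 2 paragraph of the quantitative analysis covers stress, basic needs, engagement in care and "bandwidth for parenting among recipients of the cash + care". It specifies mixed models with a categorical fixed effect for time and random participant intercepts. Results are to be an average between-group difference with a 95% confidence interval, supplemented by "presenting estimated mean outcomes at each time point individually".

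**The concern.** The article's reason for keeping EPDS continuous is that change below a threshold matters. The same reasoning applies to stress and financial strain, and no reason is given for treating them differently. The planned Aim 2 summaries also suit a continuous score. A mean of quartile labels or of band numbers has no direct reading on the scale, and no ordinal model is named.

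Two things are at stake. Grouping lowers precision for measures on the pathway in the conceptual model, from cash through lower stress and better-met needs to health. A real shift can also stay hidden inside a band, or, depending on where the quartiles are cut, be removed by the coding itself.

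**Working it through.** **1. The article's own power figure.** The only one is for EPDS (Power and sample size). Inputs: 164 and 117 participants, SD 6.24, two follow-up observations, within-participant correlation 0.5, two-sided alpha 0.05, 80% power.

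Minimum detectable difference = (1.96 + 0.8416) × 6.24 × √((1 + 0.5)/2) × √(1/164 + 1/117) = 1.83. The article states 1.8. Correlations of 0.4 and 0.3 give 1.77 and 1.71 (stated 1.8 and 1.7), and 123 and 88 participants after dropout give 2.11 (stated 2.1). These figures reproduce. None is given for PSS or financial wellbeing, so the losses below are relative to a notional continuous analysis with 80% power.

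**2. Information kept by quartile scoring.** For a normal score grouped into categories scored 0, 1, 2, …, the efficiency relative to the continuous score under a small shift is

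E = (sum of normal densities at the cut-points)² / variance of the category score.

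Quartile cuts are at −0.6745, 0 and 0.6745, with densities 0.3178, 0.3989 and 0.3178, summing to 1.0345. Four equal categories have variance 1.25. So E = 1.0345² / 1.25 = 0.856.

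- Power: Φ(2.8016 × √0.856 − 1.96) = 0.74.
- Detectable difference: multiplied by 1/√0.856 = 1.08.
- Sample size to compensate: multiplied by 1/0.856 = 1.17.

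**3. Information kept by the PSS bands, if they are what is modelled.** Cuts fall at 13.5 and 26.5. The article gives no PSS mean or SD, so a range is assumed. For example, mean 20 and SD 7 put the cuts at ±0.929, with density 0.259 at each and 0.177 of participants in each outer band. E = (2 × 0.259)² / (2 × 0.177) ≈ 0.76.

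| Assumed PSS mean | SD 6 | SD 7 | SD 8 |
|---|---|---|---|
| 16 | 0.706 | 0.744 | 0.767 |
| 18 | 0.707 | 0.757 | 0.784 |
| 20 | 0.706 | 0.761 | 0.790 |
| 22 | 0.707 | 0.757 | 0.784 |

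Across this range 80% power becomes about 65–70%, and the detectable difference rises by about 13–19%.

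Steps 2 and 3 compare independent groups at one time. Coarsening also lowers the within-participant correlation, so the loss is somewhat larger for change within participants and somewhat smaller for a between-group comparison of averaged follow-up scores.

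**4. Where the quartiles are cut.** If they are recomputed at each survey in the analysed sample, about a quarter of participants fall in each category every time. The mean quartile score is then always about (1 + 2 + 3 + 4)/4 = 2.5. A simulation (164 and 117 participants, three surveys, correlation 0.5, 2,000 replicates) gives the change in mean quartile score from baseline to the last survey:

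| True improvement | Quartiles cut | Recipients | Care only | Group difference at last survey |
|---|---|---|---|---|
| 0.5 SD in both groups | each survey, both groups | 0.00 | 0.00 | 0.00 |
| 0.5 SD in both groups | each survey, recipients only | 0.00 | 0.00 | 0.00 |
| 0.5 SD in both groups | once, pooled baseline | 0.51 | 0.51 | 0.00 |
| 0.5 SD in recipients only | each survey, both groups | 0.21 | −0.30 | 0.51 |
| 0.5 SD in recipients only | each survey, recipients only | 0.00 | −0.51 | 0.50 |
| 0.5 SD in recipients only | once, pooled baseline | 0.51 | 0.00 | 0.51 |

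Cutting within recipients at each survey removes their time effect whatever the truth. Cutting on both groups together distorts change within each group but leaves the between-group difference intact.

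**The case against.** The strongest reply is that the worst harm depends on something the article does not say. A reader might infer that the plan's quartiles erase any change over time. The article does not support that: it names neither the sample nor the survey that sets the cut-points, and a source is cited that may supply them. An article may leave that detail to a fuller document. Even with cuts made at each survey on both groups, the between-group difference survives. This objection stands, so the zero time effect is a conditional risk and not a stated defect.

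A second reply concerns PSS. Its sentence, unlike the one on financial wellbeing, does not say the categories are for analysis. The means promised under Aim 2 would fit a continuous PSS analysis with descriptive bands. Fixed bands also cannot cancel a time trend as moving quartiles can. This stands in part: the PSS half is less certain, but no continuous PSS analysis is stated.

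Third, these might be taken for the leading Aim 2 outcomes, but the article ranks none. PSS is one of two stress scales and financial insecurity one of three basic-needs domains. The study is powered on EPDS, which stays continuous, so no stated power figure is undermined. This limits the weight of the point but does not remove it.

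**Conclusion.** The point holds in a limited form. The article fixes a quartile coding of financial wellbeing for analysis and describes only a banded PSS. Both sit poorly with the means Aim 2 is to report and with the continuous handling of the other scales.

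The avoidable loss is about 14% of the information for quartiles, assuming a normal score and a small shift. It is about 21–29% for the PSS bands, which further assumes that the bands are the modelled outcome and that the mean and SD lie in the range shown. The loss of the time effect applies only if quartiles are recomputed at each survey within the recipients analysed. The effect on the trial is moderate, since the powered outcome is untouched. The change is worth making because it is nearly free.

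**What to change.** State that the PSS score (0–40) and the financial wellbeing score are analysed as continuous outcomes in the Aim 2 mixed models. Baseline should be one of the modelled time points, as in the Aim 3 EPDS model, and should not also enter as a covariate, which would put the same value on both sides of the model.

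Report the three PSS bands descriptively. If financial wellbeing quartiles are shown, define the cut-points once, from the baseline scores of both groups combined, and apply them unchanged at every survey.

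No new data are needed, because both scores exist before they are grouped. The cost is a change of wording and minor analysis work.
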